### Management and safety monitoring

Prior to the study, research team members will receive a training program, which will cover the research design, procedure, evaluation of outcome measures, randomization, data collection, and data monitoring. For example, data recorders will be trained on how to collect and manage data to ensure the objectivity, quality, and safety of data as far as possible. Patients were anonymous throughout the trial. All subject’s personal information will also be stored in a separate envelope. It will then be saved in a Microsoft Access (Microsoft Office 2010, Redmond, WA, USA) database, which is password protected [23]. A separate code was generated by pre-randomization and kept by the project manager. It is a unique identifier that identifies anonymized data. With the consent of the project leader, only members of the research team have access to the collected information for a reasonable reason [24]. Another Microsoft Access database will be used to store all trial data. It can only be got by the data collectors, the investigator, and the DMSMC. It is necessary although the APP treatment was the least risky. It consisted of the project manager, principal researcher and physician of each sub-center, and experts from the Ethics Committee of Ningxia Medical University. They are primarily responsible for the quality control of clinical trials, including but not limited to the data collection and management and uniform training for investigators. Regular monitoring and auditing data will be also required. It should be also noted that the trained data collectors and investigators are fixed and that data quality control is carried out through double-entry bookkeeping by them [23, 24]. In addition, information on patients with withdrawal will not be included in the final analysis, and other researchers will investigate what led them to withdraw from the trial. According to previous studies, the side effects of this intervention have been reported rarely. Conducting an interim analysis or stopping rules will not be applied to the current study. All of the study subjects were elderly patients, so they will be closely monitored as part of the standard of care before, during, and after study participation.

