### Interventions

The intervention group will be planned to receive auricular-plaster therapy, with one piece of Semen Vaccariae® (about 2 mm in diameter, Taicheng Technology and Development Co., Ltd., Shanghai, China) attaching to the center of a piece of medical adhesive tape (6 mm × 6 mm). This study initially selected four active acupoints including shenmen (TF4), subcortex (AT4), adrenal (TG2P), and two auricular points corresponding to pain sites based on the Nogier auricular point diagram for managing pain [22]. A researcher will bring the required items to the participants’ bedside and assist them in taking the position that is easy to operate. Subsequently, the researcher holds the helix with the left hand and identifies sensitive points by virtue of an ear probe with the right. The medical adhesive tapes with Semen Vaccariae® will be pasted on the selected auricular points with forceps by the researcher after checking and sterilizing the skin of the patients’ ears using 75% alcohol. Then, each auricular point will be pressed gently 2 times lasting 1 min each time. There is no time interval during the operation unless adverse reactions occur or until finishing the procedure. The pressure should be moderate and enough within individual’s endurance (the subject feels swelling pain, numb, and warm sensation). After the whole intervention, these tapes will be removed. However, these five points (kidney, CO10; ocuiput, AT3; internal ear, L06; external ear, TG1u; adrenal gland, TG2P) were selected in the control group. The main effect of these five points was to delay hearing loss; its procedures are described in the intervention group. However, the subject simply experiences the warm sensation in their ears. Relevant concomitant care is permitted during the trial. Although adverse reactions associated with auricular acupressure are rare, in this study, if they occurred (side effects occur during the implementation, they are short-lived and mild [15, 16]) or the participant’s requirements that the intervention they receive be discontinued, researchers can determine whether the trial will continue. Furthermore, the reasons for the withdrawal will be logged. Strategies to improve adherence to intervention protocols will be applied in *Trials*. Prior to the protocol, researchers will describe the method and duration of the intervention and the potential risk involved to the participants in detail [23]. In the intervention, there are many patients’ physiological parameters monitored by the data collector. A supervised compliance form (SAF) for this study protocol is necessary to collate patient compliance [23].

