
### Randomization and blinding

Sequence numbers of the patients with dementia will be generated by a computer-produced random list, which is performed by a statistical expert from Ningxia Medical University. But she is independent of the trial. The randomization schedule in a sealed envelope will be kept in a dedicated research office. There are many strategies to ensure the concealment of data distribution and minimize selection bias as well as create a double-blind environment. It will be blind to the randomized lists for participants (e.g., other researchers, patients, and caregivers) except the investigator responsible for conducting the intervention [24]. The project manager can suspend blinding until all the trials have been carried out according to the rules. The research team is responsible for reducing the rate of loss of intervention. Prior to the trial, the researcher went into the nursing home and lived and worked with the caregivers of the elderly to learn about the patient’s lifestyle. Meanwhile, they obtained their and their caregivers’ support and cooperation. Patients and their caregivers will be presented face to face with detailed information, which includes intervention process, collection and use of data and biological specimens, benefits, and potential adverse reactions from the trial [23]. But patients also have the right to withdraw from the study at any time without affecting subsequent care. In case patients and (or) their caregivers decide to quit the trials, data and biological specimens will be destroyed. It has been also documented in the informed consent form.

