### Sample size estimation

After obtaining the ethical approval of our study protocol, a preliminary experiment with a sample size of 30 was conducted in Nursing Home, Yinchuan, in January 2020. The results of the pilot study indicated that the FPS-R score of the control group and the intervention group was 5.97 ± 1.81 and 4.79 ± 1.96, respectively. We have consulted a statistician from the School of Medical Statistics and Epidemiology at Ningxia Medical University, who finished the randomization list of the recruits. With a type 1 error rate of 0.05 (*α* = 0.05, two-tail) and a 90% power (*β* = 0.10), the sample size of the study scheme was calculated by the statistical expert, which was 86 patients in each group. According to our study design and considering the particularity of this research subject (they are less likely to complete the entire experiment), we assume a 20% drop-out rate. The total sample size of 206 cases (per group was 103 cases) is required to reduce the underpower of the study.

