### Data statistical analysis

On the basis of the intention-to-treat (ITT) principle, SPSS version 22.0 (Chicago, IL, USA) will be recommended to run the data statistical analysis on both the real APP group and the sham APP group. Information on all patients in the random list should be included in the final analysis. If data is missing, the missing data imputation should be used to analyze the validity of the statistical analysis. The statistical description of categorical variables (the population demographic data) will be mainly presented by the relative number (rate, proportion, and ratio). The continuous variables (repeated measurement data of three physiological parameters) will be compared by analysis of variance (ANOVA) or the Kruskal-Wallis test (or chi-squared tests) for the two groups. Other categorical variables (data on satisfaction from caregiver, acceptance from patient, and additional use of analgesics) will be described by the nonparametric test (Wilcoxon’s rank sum test). A two-sided *P* value < 0.05 will be considered to be statistical significance. Therefore, subjects’ personal information, such as nationality, education, and medication history, will be used to consider whether to perform statistical analysis in subgroups.

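### The protocol puts every randomised patient in the final analysis under ITT, but elsewhere excludes withdrawn patients from it and destroys the data of those who quit

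*Protocol article*

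**What the plan says.** Three places in the protocol article bear on who is analysed.

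- **Data statistical analysis.** The analysis runs "On the basis of the intention-to-treat (ITT) principle". The section adds: "Information on all patients in the random list should be included in the final analysis". It then provides for gaps: "If data is missing, the missing data imputation should be used to analyze the validity of the statistical analysis". No imputation method is named, which an article may leave to a fuller document.
- **Management and safety monitoring.** Here "information on patients with withdrawal will not be included in the final analysis". Nothing limits this to a per-protocol or sensitivity set, or to patients who leave before randomisation.
- **Randomization and blinding.** "In case patients and (or) their caregivers decide to quit the trials, data and biological specimens will be destroyed". The protocol adds of this arrangement: "It has been also documented in the informed consent form".

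Two further places give context. Interventions allows a session to be discontinued after an adverse reaction or at the participant's request, and says "the reasons for the withdrawal will be logged". Sample size estimation says "we assume a 20% drop-out rate".

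**The concern.** The inclusion rule and the exclusion rule both govern the final analysis, and both cannot be followed. Whoever analyses the trial can point to text for either population, possibly after seeing the results.

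The choice matters because withdrawal happens after randomisation. Interventions describes different sensations in the two arms: true pressing goes on to a swelling ache, numbness and warmth, while sham pressing gives warmth alone. Stopping can follow an adverse reaction or a request. The number and kind of patients who leave may therefore differ by arm, and comparing only those who stay would no longer be the randomised comparison.

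The destruction rule goes further. A later analysis plan could choose ITT, but it could not restore scores already destroyed. For a patient who quits, imputation would have little to work from beyond the allocated arm.

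**Working it through.** **1. The rules side by side**

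| Patient | Data statistical analysis | Management and safety monitoring | Randomization and blinding |
|---|---|---|---|
| Stays in, has a missing T1 or T2 score | in, imputed | not addressed | data kept |
| Withdraws, but neither patient nor caregiver decides to quit (for example, researchers stop the session) | in, imputed | out, if counted as withdrawn | destruction not clearly triggered |
| Patient or caregiver decides to quit | in, imputed | out | data destroyed |

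The conflict covers the last row and, depending on how withdrawal is read, the middle one. ITT with imputation remains possible for the first row.

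**2. The plan's own sample-size figures**

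Inputs from Sample size estimation: 86 per group, 20% drop-out, 206 in total, two-sided α 0.05, power 90%, pilot scores 5.97 ± 1.81 and 4.79 ± 1.96.

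- Drop-out step: 86 × 1.2 = 103.2, so 103 per group and 206 in total. This reproduces.
- The 86 does not. With SD² = (1.81² + 1.96²)/2 = 3.559 (SD 1.886) and difference 1.18, n = 2 × (1.960 + 1.282)² × 3.559 / 1.18² = 53.7, so 54 per group. That is a separate matter, and nothing below depends on it.

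**3. Patients affected if all drop-out were withdrawal**

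- 206 × 0.20 = 41.2, so up to about 41 patients.
- Remaining: 206 − 41 = 165. Per group: 103 × 0.8 = 82.4, so about 82, below 86.
- Power: the difference that 86 per group detects with 90% power at SD 1.886 is 1.886 × √(2/86) × 3.242 = 0.93. At 82 per group, power is Φ(0.93 / (1.886 × √(2/82)) − 1.96), about 88.6%.

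The loss of power is small. The problem is bias.

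**4. Possible bias from exclusion**

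The documents give no withdrawal rates by arm and no link between pain and withdrawal, so both are assumptions here. Model: no true effect, 103 per arm, SD 1.89, and the patients highest on a latent score leave. That latent score correlates ρ with the outcome. When a fraction p leaves, the mean of those who stay falls by ρ × SD × g(p), where g(p) = φ(z)/(1 − p) and z is the upper-p normal point. The bias (true minus sham) is −ρ × SD × [g(true) − g(sham)].

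- 20% against 20%: the two terms cancel, so there is no mean bias.
- 25% against 15%: g = 0.424 and 0.274. At ρ = 0.5, −0.5 × 1.89 × 0.149 (difference before rounding) = −0.14.
- 30% against 10%: g = 0.497 and 0.195. At ρ = 0.5, −0.5 × 1.89 × 0.302 = −0.29.

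Simulation that removes a fixed number of patients per arm, followed by a t-test on those who stay, gives:

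| ρ | 25% vs 15%: bias, false positives | 30% vs 10%: bias, false positives |
|---|---|---|
| 0.3 | −0.09, 6% | −0.18, 10% |
| 0.5 | −0.15, 8% to 9% | −0.29 to −0.30, 18% to 19% |
| 0.8 | −0.24, 19% | −0.47, 42% to 44% |

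The simulated biases slightly exceed most of the formula values because whole patients are removed (26 and 15, or 31 and 10, of 103). Fixed-count removal also inflates the error rate by itself: at ρ = 0.8 it rejects about 8% even with 20% leaving each arm. If each patient instead leaves on crossing a threshold, the ρ = 0.8 rates are about 14% and 41%.

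**The case against.** The strongest reply is that the rules can partly coexist. Destruction applies only where a patient or caregiver decides to quit. A missed score, or a session that researchers stop, need not be quitting, and such patients could stay in with imputation. This stands, and it limits the point. It does not remove the conflict, because the exclusion sentence speaks of withdrawal generally and of the final analysis.

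Several stronger readings are tempting, but the documents do not support them:

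- **No ITT analysis is possible, or the trial is completers-only.** This would follow only if every incomplete patient counted as having quit.
- **About 41 records will be erased.** The assumed drop-out covers patients unlikely to complete the whole procedure, which is broader than quitting. Forty-one is an upper figure for those affected, not a forecast of erasures.
- **Adverse-reaction records are lost.** This is possible, but the text does not say whether the destroyed data include them.
- **Logging reasons contradicts destroying data.** A log of reasons can survive the destruction of outcome data.
- **The trial has a known bias.** The rates and correlations above are assumed. If patients in less pain were the ones to leave, the sign would reverse.

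It is also fair to say that the destruction clause is already in the consent form. Recruitment was expected from December 2020 to December 2021 and the article appeared in May 2022, although it still calls recruitment ongoing. Many patients may have consented under the clause, so rewording it may recover little. The conflict over the analysis set can still be resolved in full.

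**Conclusion.** The point holds as a contradiction in stated rules, not as missing detail, and needs no simulation to establish it. The declared population is all randomised patients; another section removes withdrawn patients from the same analysis; a third destroys the data of those who quit, so for them ITT could use no observed score. Patients with missing values who did not quit are not affected by the destruction rule.

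Size: up to about 41 of 206 patients, if all assumed drop-out is withdrawal. The possible bias depends on assumptions. With no true effect and ρ from 0.3 to 0.8, 25% against 15% withdrawal gives about −0.09 to −0.24 points and 6% to 19% false positives; 30% against 10% gives about −0.18 to −0.47 points and 10% to about 42%. Equal withdrawal gives no mean bias. The upper error rates partly reflect how the simulation removes patients. The passages should be reconciled before the analysis, because leaving two primary populations open allows a choice after results are known.

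**What to change.** 1. Delete the exclusion of withdrawn patients under Management and safety monitoring.
2. Under Data statistical analysis, name one primary set: all randomised patients in their allocated arm, using every score recorded before withdrawal, with imputation as that section already provides. The choice of model can sit in the analysis plan. Imputation from earlier scores reduces bias only as far as those scores predict the missing ones.
3. Keep a completers analysis, labelled as sensitivity only.
4. Amend the clause under Randomization and blinding, and the consent form, prospectively: data recorded up to withdrawal, including adverse reactions, are kept unless the patient asks for erasure.
5. Honour consents already signed under the destruction clause.
6. Report withdrawals and erased records by arm, so that readers can judge any imbalance.

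Cost: a protocol and consent amendment with ethics review, and no extra patients. Records already destroyed, and those that must still be destroyed under signed consents, stay lost.

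### Withdrawn patients are excluded in one section, while another requires an ITT analysis of everyone on the random list; both rules cannot be followed

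*Protocol article*

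**What the plan says.** Two sections of the protocol article set the primary analysis population, and they set it differently.

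- Management and safety monitoring: "information on patients with withdrawal will not be included in the final analysis". The same sentence adds that other researchers will look into why these patients left the trial.
- Data statistical analysis: the analysis follows ITT, "Information on all patients in the random list should be included in the final analysis", and "If data is missing, the missing data imputation should be used".

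Three further places bear on who counts as withdrawn.

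- Interventions: after an adverse reaction, or if the participant asks that "the intervention they receive be discontinued, researchers can determine whether the trial will continue. Furthermore, the reasons for the withdrawal will be logged". The same section says "There is no time interval during the operation unless adverse reactions occur", which allows a pause.
- Randomization and blinding: if patients or their caregivers "decide to quit the trials, data and biological specimens will be destroyed", and "It has been also documented in the informed consent form".
- Sample size estimation: these patients are described as "they are less likely to complete the entire experiment), we assume a 20% drop-out rate".

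**The concern.** The two population rules refer to the same final analysis. The article names no per-protocol or secondary set to which the exclusion could belong. A randomized patient who withdraws is therefore both in and out, and the choice could be made after the results are known.

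If the exclusion is applied, patients are removed from the FPS-R comparison after randomization. That can bias the difference between arms if withdrawal is more frequent in one arm, or if withdrawn patients differ from completers by a different amount in each arm. Unequal withdrawal is plausible but not documented. The Interventions section describes swelling pain and numbness as target sensations only in the true arm, and warmth alone in the sham arm. The investigator who delivers the session knows the allocation, so a decision on whether to continue may not be blind. On the other side, the section describes the pressing as gentle and side effects as rare, brief and mild.

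The Interventions section adds an ambiguity. It speaks of logging reasons for withdrawal directly after describing a discontinued intervention. A patient who stops the session, still consents and can give an FPS-R score is kept under the ITT rule, but the patient's status under the exclusion rule is unclear.

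**Working it through.** **1. The rules side by side**

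| Randomized patient | Management and safety monitoring | Data statistical analysis | Randomization and blinding |
|---|---|---|---|
| Quits the trial | Left out | Kept, imputed if missing | Data destroyed |
| Researchers decide not to continue | Left out, if this counts as withdrawal | Kept, imputed if missing | Not covered |
| Stops the session, still consents | Unclear | Kept | Not covered |

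The first row is a plain contradiction. The other two rows depend on what withdrawal means, which the article does not define.

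**2. How many patients**

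Inputs from Sample size estimation: 86 per arm before drop-out, 20% drop-out, 103 per arm, 206 in total.

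- The plan's own inflation reproduces: 86 × 1.2 = 103.2, so 103 per arm and 206 in total. The 86 is taken as stated. The usual two-mean formula with the pilot figures gives 54 per arm, but that is a separate matter and does not enter here.
- Loss that the design allows for: 103 − 86 = 17 per arm (16.5%), or 34 in total.
- Loss at the stated rate: 0.20 × 206 = 41.2, about 41.

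The exclusion could therefore reach 34 to 41 patients, leaving 172 to 165 analysed instead of 206. How many of these would be stopped sessions with a score still obtainable is not stated.

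**3. Bias**

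Let a fraction p of an arm be excluded, and let excluded patients score g points worse than completers. The full-arm mean is the completers' mean plus p × g, so exclusion lowers the arm mean by p × g. With the same g in both arms:

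bias in the difference = (p_true − p_sham) × g

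The values of p and g below are assumptions, chosen to average 20% exclusion.

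**4. Type I error**

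- Pilot SDs (Sample size estimation) are 1.81 and 1.96; pooled SD = √((1.81² + 1.96²)/2) = 1.886.
- At 25% against 15%, about 77 and 88 patients remain: SE = 1.886 × √(1/77 + 1/88) = 0.294. At 22.5% against 17.5%, about 80 and 85 remain, and the SE is again 0.294.
- Type I error = P(|Z + bias/SE| > 1.96).

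| Excluded, true / sham | Gap g | Bias | Type I error |
|---|---|---|---|
| 20% / 20% | any, equal in both arms | 0 | 5.0% |
| 22.5% / 17.5% | 1 to 2 points | 0.05 to 0.10 | 5.3% to 6.3% |
| 25% / 15% | 1 to 2 points | 0.10 to 0.20 | 6.3% to 10.4% |

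The pilot difference is 5.97 − 4.79 = 1.18, so a bias of 0.20 is 0.20/1.18 = 17% of it. In these scenarios the bias favours true acupressure.

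**5. Does keeping everyone cost power?**

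Suppose 20% of the true arm gained nothing: 0.8 × 1.18 = 0.944. With 103 per arm, SE = 1.886 × √(2/103) = 0.263; 0.944/0.263 = 3.59; power is about 95%, against 90% planned. This assumes the pilot difference and SD, and a score for all 206 patients. Some scores will in fact be lost or imputed, so it is an idealised figure. It does show that the issue is bias and not power.

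**The case against.** The strongest objection concerns scope. A reader might infer that the protocol drops everyone whose session is stopped. The documents do not support that. The exclusion sentence itself goes on to speak of leaving the trial, and Study design and Randomization and blinding also use withdrawal to mean leaving the study. The Interventions section neither defines withdrawal nor mentions analysis. It allows a pause and lets researchers decide whether to go on, so its mention of withdrawal may cover only the cases where they decide against. This objection stands: the status of stopped sessions is an ambiguity, not a stated exclusion.

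The second objection is that the magnitude overstates what a rewrite would gain. This also stands. The 34 to 41 patients are all planned drop-outs, and those who withdraw consent stay out under any acceptable rule. Bias is linear in the excluded fraction: if, as an assumption, half of the difference between arms came from withdrawn consent, the rewrite would remove only half of each bias shown. A reader might also take 10.4% as the expected error rate. It is the top of an assumed range, and no document gives withdrawal by arm or scores of withdrawn patients.

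Neither objection touches the core. Even on the narrowest reading, in which only patients who quit are excluded, the ITT sentence allows no exception and so conflicts with both the exclusion and the destruction rule.

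**Conclusion.** The contradiction is real and rests on the text alone. The exclusion of withdrawn patients and the ITT rule for everyone on the random list cannot both govern the final analysis. The destruction of data from patients who quit also conflicts with the ITT rule as worded. Whether a consenting patient who stops the session would be excluded is unclear.

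Up to 34 to 41 of 206 patients are affected at the planned drop-out. The bias is zero if exclusion and gap are equal in both arms, and reaches 0.10 to 0.20 FPS-R points (type I error 6.3% to 10.4%) under an assumed 25% against 15% exclusion with a gap of 1 to 2 points. These figures are an upper bound in that they count the whole planned drop-out, of which the fix recovers only a part; they are not a ceiling over every conceivable rate and gap. The text should be changed, but the documents do not show that the trial's result will be materially biased.

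**What to change.** - Management and safety monitoring: replace the exclusion with a statement that only patients who withdraw consent for use of their data are left out, and that numbers and reasons are reported by arm.
- Data statistical analysis: name that single exception to the all-randomized rule, and apply the planned imputation to other missing FPS-R scores.
- Interventions, and Randomization and blinding: state that stopping a session is not quitting the trial. Patients who stop but still consent are rated at T2, 5 minutes after the session ends, and at T1 only if the session reached 5 minutes, since T1 is defined during the intervention. They are analysed in the arm to which they were allocated. The destruction rule stays as it stands in the consent form.

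Cost: short text changes in four sections, one or two brief ratings in patients who stopped, some imputed scores, and an estimate that includes incomplete sessions. Recruitment was ongoing at publication, so the change would go to the ethics committee, the monitoring committee and the participants, as Study design provides for important modifications.
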